There has been considerable recent interest in the role of vitamin D in maternal and infant health outcomes in low-income settings [29]. Some observational studies have suggested that antenatal vitamin D deficiency increases the risk of adverse pregnancy and birth outcomes, including SGA [30, 31]. However, there is scant evidence from controlled clinical trials [31, 32], and the World Health Organization (WHO) recently advised against routine vitamin D supplementation in pregnancy until further data become available [33]. Building on our earlier findings of a beneficial effect of prenatal vitamin D supplementation on infant length in a preliminary trial [26], we are conducting a larger dose-ranging trial of maternal vitamin D_3_ supplementation in Dhaka, Bangladesh. The primary aim is to investigate the effect of maternal vitamin D supplementation on infant length at 1 year of age, but the trial also provides an opportunity to study a range of other potential vitamin D–responsive outcomes.

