#### Supplement administration

Supplementation begins at enrollment (second trimester) and continues on a weekly basis throughout pregnancy and the postpartum period until 26 weeks postpartum (6 months). Study personnel maintain and store all tablet supplies in locked study offices and directly observe tablet ingestion during home or clinic visits. However, for periods of up to 4 weeks during which the participant plans to travel or during holidays, advance doses may be given to the participant to take unobserved but with telephone reminders. Tablets are swallowed whole with any liquid (e.g., water, juice, tea) or, if necessary, chewed with or without a small amount of soft food. Tablets may be consumed with or without food, which has a negligible impact on vitamin D absorption [44]. Although scheduled for specific 7-day intervals, a missed dose may be administered as a late dose on any day up to 7 days after the scheduled date of administration; thereafter, subsequent dosing continues as originally scheduled, even if this incurs at an interval of less than 7 days between the late dose and the subsequent regularly scheduled dose. If a participant refuses a dose or complains of feeling unwell (e.g., nausea) on the scheduled day of dose administration, the dose may be deferred for up to 7 days. If a participant vomits during or within 20 minutes of dose administration (observed by study personnel), the dose may be repeated immediately or may be deferred to another day (within 7 days). If vomiting occurs more than 20 minutes after a dose was swallowed, the dose is considered successfully administered. If a participant refuses doses for 3 consecutive weeks and in the third week expresses the intention to continue avoidance and/or refusal of the dose, weekly supplementation may be discontinued, but clinical follow-up and scheduled data collection procedures may continue.

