### Visit schedule

Following enrollment and randomization of pregnant women at 17–24 weeks of gestation, weekly supplementation (vitamin D or placebo) occurs throughout the prenatal period and during the first 6 months postpartum. Data collection continues during the non-intervention phase beginning at 26 weeks postpartum. The primary anthropometric outcome will be ascertained at 1 year of age, and follow-up of infants will continue until 2 years of age. The prenatal timeline of study activities is structured in terms of GA (in weeks), based on the recalled LMP and/or ultrasound results. Postnatal follow-up visits are scheduled on the basis of the infant’s age in weeks (rather than anniversaries of the birthdate); however, the timing of major visits is operationally described in terms of months or years for simplicity (e.g., 3 months = 13 weeks, 6 months = 26 weeks, 9 months = 39 weeks, 1 year = 12 months = 52 weeks, and 2 years = 24 months = 104 weeks).

Participant visits are scheduled on a weekly basis during the prenatal and 6-month postpartum intervention phase. The majority of visits are conducted in the participants’ homes; however, selected visits that involve specimen collection or anthropometry are preferentially conducted in a clinic at MCHTI. Participants are strongly encouraged to seek a facility-based delivery at MCHTI; however, perinatal data and specimen collection are attempted when feasible for home deliveries or for deliveries that occur at facilities other than MCHTI. Beyond 6 months, clinic-based visits occur at 3-month intervals until 2 years of age (Additional file 2). Participant retention is promoted through frequent interaction between field-level study personnel and the participants (weekly during the intervention phase). Adherence to the schedule of clinic visits is facilitated by compensation of participants for costs of transportation and time away from the home and/or work.

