In the primary analyses, an intention-to-treat (ITT) approach will be used, meaning participants will be considered exactly as randomized, regardless of supplementation adherence or completeness of follow-up and without adjustment for baseline covariates, and also without imputation for missing data; that is, infants for whom LAZ is unavailable at 1 year of age will be excluded from the analysis. However, because the trial is aimed at establishing a biological mechanism of effect, per-protocol analyses will also be performed by restricting to participants who consumed at least 90 % of all scheduled doses. Conventional ITT analyses of postnatal growth outcomes typically disregard between-individual variations in GA at birth; however, because the WHO-GS was based on a full-term cohort [54], this may lead to differential misclassification of preterm infants with respect to LAZ if length is plotted on the growth chart using the chronological age. Although we plan to follow the convention in the primary analysis, we will perform a sensitivity analysis in which LAZ will be assigned to preterm infants using the age corrected for GA at birth (rather than chronological age). Several other sensitivity analyses are planned. Multivariable adjustment will be used for covariates that substantially differ across groups at baseline. A missingness analysis will be performed to understand the pattern of missing data (in particular to detect differential loss of data across groups), and multiple imputation methods will be used in sensitivity analyses to correct for these losses. Subgroup and interaction analyses will be based on the following covariates: GA at birth, infant sex, maternal baseline vitamin D status, maternal height, and maternal supplement adherence.

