Clinical events will be monitored and documented by study physicians, and serious adverse events will include all deaths and hospitalizations (with the exception of admissions to the hospital for uncomplicated vaginal or cesarean delivery). The only clinical events that will routinely lead to discontinuation of study supplementation are those adverse events that are ascertained to be supplement-related or the diagnosis of a medical condition that potentially or theoretically increases sensitivity to vitamin D supplementation following clinical review by the Trial Steering Committee (TSC): confirmed hypercalcemia (see definition above), symptomatic vitamin D deficiency diagnosed by a study physician or consultant physician (e.g., osteomalacia), fetal or infant death, or onset of a medical condition or initiation of a medication following enrollment that may reasonably predispose to vitamin D sensitivity, altered vitamin D metabolism, and/or hypercalcemia (e.g., tuberculosis or therapy for tuberculosis, sarcoidosis, renal and/or ureteral stones, parathyroid disease, renal or liver failure, or use of anticonvulsants). The occurrence of a serious adverse event, in of itself, will not automatically lead to study supplementation cessation.

Research ethics committee/institutional review board approval was obtained from the Hospital for Sick Children Research Ethics Board (REB1000039072) and the ICDDR,B Ethical Review Committee (ERC; PR number 13055). A DSMB was created by the ERC of ICDDR,B. An external international member of the TSC reviews reports submitted to the DSMB and reports to the TSC. There are no formal interim analyses of efficacy or stopping rules planned for this trial.

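### For the prenatal dose contrasts, two of the five planned subgroup factors (gestational age at birth and supplement adherence) arise after randomisation, so those subgroup results are not randomised comparisons

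*Protocol article*

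**What the plan says.** The Statistical analysis section of the protocol article lists five factors in one sentence: "Subgroup and interaction analyses will be based on the following covariates: GA at birth, infant sex, maternal baseline vitamin D status", followed by maternal height "and maternal supplement adherence". It gives the five equal standing. It does not separate factors fixed before randomisation from those that arise later, and it does not say which treatment contrasts the list serves.

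The Visit schedule section sets the timing: "Following enrollment and randomization of pregnant women at 17–24 weeks of gestation, weekly supplementation (vitamin D or placebo) occurs throughout the prenatal period". The Supplement administration section has dosing run from enrolment to 26 weeks postpartum.

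There are two primary aims (Objectives; Statistical analysis). The first is five prenatal comparisons: each dose against placebo, and adjacent doses against each other. The second compares 28,000 IU/wk with placebo postpartum among women who all received 28,000 IU/wk prenatally.

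**The concern.** A subgroup contrast keeps the protection of randomisation only if treatment cannot influence who falls in the subgroup. If it can, the women in a given stratum of one arm differ systematically from those in the same stratum of another arm. The contrast then mixes treatment effect with selection.

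Gestational age at birth carries a second cost. If prenatal vitamin D lengthened gestation and this improved length, stratifying on gestational age would remove that part of the effect.

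The trial describes itself as aimed at a biological mechanism, so a claim that vitamin D works only in term infants, or only in adherers, would attract attention. Neither claim would rest on a randomised comparison.

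**Working it through.** **Step 1: place each factor in time.**

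| Factor | Prenatal contrasts | Postpartum contrast |
|---|---|---|
| Infant sex | fixed at conception | fixed at conception |
| Maternal baseline vitamin D status | before randomisation | before randomisation |
| Maternal height | not changed by treatment | not changed by treatment |
| Gestational age at birth | after randomisation and dosing | before the arms diverge |
| Adherence, prenatal part | after randomisation | before the arms diverge |
| Adherence, postpartum part | after randomisation | after the arms diverge |

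Three of the five factors are safe for every contrast. The other two are post-randomisation for the prenatal contrasts. For the postpartum contrast only adherence after delivery is affected.

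**Step 2: could treatment change them, on the document's own account?**
- *Birth outcomes.* The Background says: "Some observational studies have suggested that antenatal vitamin D deficiency increases the risk of adverse pregnancy and birth outcomes, including SGA". This makes an effect on birth outcomes plausible, but the outcome it names is size for gestational age. Gestation length is not named.
- *Adherence.* Under Participant safety monitoring, supplementation stops for supplement-related events, including confirmed hypercalcemia, and for symptomatic vitamin D deficiency. Either could differ by dose. The same section expects no true hypercalcemia.

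**Step 3: size for gestational age.** The documents give no preterm rate and no correlations, so all inputs here are assumptions. Treatment has no effect on length-for-age z-score (LAZ). An unmeasured factor correlates b with gestation and g with LAZ, both 0.3 to 0.5. Preterm birth is p0 = 15% on control and p1 = 10% or 12% on treatment. All variables are normal with SD 1. With φ the standard normal density and z(p) the p-quantile:

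- False difference, preterm = b·g·[φ(z(p0))/p0 − φ(z(p1))/p1]
- False difference, term = b·g·[φ(z(p1))/(1−p1) − φ(z(p0))/(1−p0)]

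φ/p is 1.554 at 15%, 1.667 at 12% and 1.755 at 10%. φ/(1−p) is 0.274, 0.227 and 0.195.

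- Preterm, smallest: 0.09 × (1.554 − 1.667) = −0.010 z
- Preterm, largest: 0.25 × (1.554 − 1.755) = −0.050 z
- Term, smallest: 0.09 × (0.227 − 0.274) = −0.004 z
- Term, largest: 0.25 × (0.195 − 0.274) = −0.020 z

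Simulation with two million subjects agrees within simulation error. A second simulation assumed a stronger link between the unmeasured factor and gestation (correlation 0.65) and a gain of 0.2–0.6 weeks. It gave −0.02 to −0.08 z in preterm and −0.01 to −0.03 z in term infants. With no shift in gestation the difference was about zero.

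**Step 4: compare with sampling error.** The Design and sample size section has 220 analysable infants per group. At 15% and 10–12%, that is 33 against 22–26 preterm infants. With SD near 1 (assumed; the article states no SD):

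- Standard error, preterm = √(1/33 + 1/22) = 0.28, or √(1/33 + 1/26) = 0.26
- Standard error, term (187 against 198) = √(1/187 + 1/198) = 0.10

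The largest bias is about one fifth of a standard error in each stratum: 0.050/0.28 and 0.020/0.10.

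**Step 5: adherence.** A simulation with no true effect, about 80% adherence, and frailty-related stopping in the vitamin D arm only (log-odds 0.3 to 1.0 per SD) gave +0.02 to +0.10 z in adherers and −0.07 to −0.33 z in non-adherers. The overall difference was about zero. Adherence shares differed by only about 0.4 to 4 percentage points, so similar overall adherence does not show that adherers are comparable. Nothing in the document supports stopping of this one-sided kind. These figures show what could happen and are not an estimate.

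**The case against.** A reader might infer that the two factors are invalid throughout and should be deleted. The documents do not support that. In the postpartum comparison both arms take the same prenatal dose, and participants, field staff and investigators are blinded. The postpartum allocation cannot affect gestational age at birth or prenatal adherence, so both are legitimate modifiers there. This part of the objection stands, and it limits the point.

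A reader might also infer that gestation length is an expected treatment effect, or that hypercalcemia stops will make adherence differ by dose. Neither is shown. The Background names size for gestational age, and no true hypercalcemia is anticipated. Tablets are identical in appearance and taste, ingestion is mostly observed directly, and masking limits differential adherence. The argument rests on what treatment could change, not on what the document predicts.

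It can be added that these are supplementary analyses, that the list says covariates without calling all of them baseline, and that labelling is often left to the analysis plan. This is fair as to importance. But the article fixes the list itself and puts both kinds of factor on one footing. A separately labelled per-protocol analysis, at 90% or more of scheduled doses, already covers adherers, so an adherence subgroup beside true baseline modifiers invites reading a non-randomised contrast as effect modification.

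**Conclusion.** The point holds for the prenatal dose contrasts on gestational age at birth and adherence, and for the postpartum contrast on adherence after delivery only. It follows from timing and needs no numerical assumption.

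The size does rest on assumptions. Bias arises only if treatment shifts the factor and something else links the factor to LAZ. For gestational age, at 15% falling to 10–12% preterm, it is at most about 0.05 z (0.08 z under the stronger assumptions), which is small beside the stratum's sampling error. This bias alone would seldom produce a false subgroup claim. For adherence neither size nor direction can be known in advance.

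It would be wrong to infer that the primary result is at risk. The primary analysis takes participants as randomised, whatever their adherence, and without covariate adjustment. No sample size, α or power figure changes. This is a worthwhile, low-cost correction to secondary analyses.

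**What to change.** - **Prenatal contrasts:** limit subgroup and interaction tests to infant sex, maternal baseline vitamin D status, maternal height and, if wanted, gestational age at enrolment.
- **Gestational age at birth, prenatal contrasts:** analyse it as an outcome or mediator. Keep the planned sensitivity analysis that uses age corrected for gestation.
- **Adherence, prenatal contrasts:** replace the subgroup with a complier-average estimate that uses randomisation as the instrument. State its assumptions, in particular that allocation acts on LAZ only through doses taken. Otherwise report the subgroup only as exploratory and non-randomised.
- **Postpartum contrast:** gestational age at birth and prenatal adherence may stay as modifiers. Treat postpartum adherence as in the prenatal contrasts.
- **Wording:** say which contrast each factor applies to, and over which period adherence is counted.

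The cost is analysis-plan text only. No new data are needed.

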### Participant safety monitoring

Participant safety during the intervention phase is monitored by study personnel based on (1) a checklist of maternal symptoms that may indicate vitamin D toxicity or other medical concerns during weekly follow-up visits, (2) passive and active monitoring for maternal and infant clinical events, and (3) maternal serum calcium measurement at scheduled intervals during the intervention phase (baseline, 30 weeks of gestation, delivery, 3 months postpartum, and 6 months postpartum). Secondary safety measures include infant serum calcium measurement at 3 and 6 months of age and maternal urinary calcium:creatinine at the time of delivery.

Serum calcium is the best available biomarker of vitamin D toxicity [57, 58]; therefore, hypercalcemia is the primary biochemical safety outcome. Nonetheless, on the basis of our own experience with doses equivalent to up to 5000 IU/day (see above) and previously published trials conducted in the United States using doses up to 4000 IU/day during pregnancy [43] and up to 6400 IU/day during lactation [59], we do not anticipate any episodes of true hypercalcemia or other supplement-related adverse events.

*Possible hypercalcemia* is defined as a single serum calcium concentration above 2.60 mmol/L. This threshold is based on a conservative upper limit of the normal range that accommodates expected variation in serum calcium throughout pregnancy [60], but it avoids the unnecessary operational complexity of using a normal range that varies by stage of gestation. Any participant with possible hypercalcemia detected through scheduled blood sampling (or at the time of a clinical serious adverse event; e.g., hospitalization) will be asked to provide a second sample within 24 h of the time that the study physician receives a report of an abnormal value. Abnormal serum calcium results will always be reported and confirmed before the time of the following week’s supplement dose (to enable a decision to be made about withholding supplementation). Severe derangements in serum calcium will be managed as urgently as possible, including referral for hospitalization.

*Confirmed hypercalcemia* is defined as serum calcium concentration above 2.60 mmol/L in two consecutive specimens and will be considered the primary supplement-related adverse event. The second, confirmatory specimen is required owing to the possibility of a laboratory error, but clinical management will not await the second assay if the participant is symptomatic. If the repeat serum calcium is normal, then supplementation will continue and a further repeat serum calcium will be measured 1 week after the first abnormal result to confirm that it remains within the normal range. In the unlikely event that a participant has confirmed hypercalcemia, study personnel will follow the clinical course until normalization of serum calcium or 1 month postpartum (whichever occurs later). Participants with mild and asymptomatic hypercalcemia may not require referral or treatment beyond the cessation of supplementation and will continue to participate in study follow-up. Participants with confirmed or suspected moderate to severe hypercalcemia (serum Ca >2.80 mmol/L and/or symptomatic) will be assessed at a hospital by a clinician with expertise in the treatment of hypercalcemia.

In previous prenatal vitamin D supplementation trials in Dhaka, we used regular monitoring of maternal urinary Ca:Cr ratio as a screening measure for vitamin D toxicity [16, 40]. However, this test is non-specific and frequently led to the need for repeat testing that was burdensome but uninformative; in no cases did an isolated Ca:Cr ratio indicate vitamin D toxicity. Therefore, regular urine Ca:Cr ratio assessment is not employed as a primary clinical safety monitoring tool in the present trial. However, we will measure urinary Ca:Cr ratio in mothers at delivery as a screening test for hypercalciuria rather than for overt vitamin D toxicity. Abnormal values (Ca:Cr ratio >1 mmol/mmol) will prompt repeat testing, and either of the following criteria will be considered a presumptive diagnosis of hypercalciuria: two consecutive urine samples with Ca:Cr ratio above 1 mmol/mmol or one urine sample with Ca:Cr ratio above 1 mmol/mmol in the presence of persistent symptoms suggestive of possible uro- and/or nephrolithiasis. Participants with persistent symptoms of renal colic or hypercalciuria will be referred for renal ultrasound to assess for the presence of urolithiasis or nephrolithiasis. Participants with uro- or nephrolithiasis will be referred for consideration by the DSMB for a decision regarding unblinding and possible discontinuation of the study supplement, which is to be decided on a case-by-case basis. Biochemical evidence of hypercalciuria alone will not trigger urgent DSMB review, but it will be reviewed at regular intervals. However, participants with hypercalciuria and an absence of stones will undergo repeat urine Ca:Cr ratio assessment 1 month after initial diagnosis. If hypercalciuria is persistent, a repeat ultrasound will be undertaken.

When caregivers permit scheduled infant blood sampling, serum calcium will be routinely measured. The normal range of infant serum calcium is higher than in adults, and normal values may be as high as 3.05 mmol/L [61–66]. However, because there are few reference data for infants specifically at 3 and 6 months, we have chosen to use a more conservative threshold of greater than 2.80 mmol/L to define above-range infant values at the 3- and 6-month visits, which will prompt repeat assessment.

Clinical events will be monitored and documented by study physicians, and serious adverse events will include all deaths and hospitalizations (with the exception of admissions to the hospital for uncomplicated vaginal or cesarean delivery). The only clinical events that will routinely lead to discontinuation of study supplementation are those adverse events that are ascertained to be supplement-related or the diagnosis of a medical condition that potentially or theoretically increases sensitivity to vitamin D supplementation following clinical review by the Trial Steering Committee (TSC): confirmed hypercalcemia (see definition above), symptomatic vitamin D deficiency diagnosed by a study physician or consultant physician (e.g., osteomalacia), fetal or infant death, or onset of a medical condition or initiation of a medication following enrollment that may reasonably predispose to vitamin D sensitivity, altered vitamin D metabolism, and/or hypercalcemia (e.g., tuberculosis or therapy for tuberculosis, sarcoidosis, renal and/or ureteral stones, parathyroid disease, renal or liver failure, or use of anticonvulsants). The occurrence of a serious adverse event, in of itself, will not automatically lead to study supplementation cessation.

Research ethics committee/institutional review board approval was obtained from the Hospital for Sick Children Research Ethics Board (REB1000039072) and the ICDDR,B Ethical Review Committee (ERC; PR number 13055). A DSMB was created by the ERC of ICDDR,B. An external international member of the TSC reviews reports submitted to the DSMB and reports to the TSC. There are no formal interim analyses of efficacy or stopping rules planned for this trial.

